
### Aims and Hypotheses

The present experiment aims at comparing the effects on cognitive and motor functions of three types of training programs (NW, CT-c, and CT-fit), which differ in the nature of cognitive-motor exercises. It is hypothesized that, while all training would induce similar physical and motor fitness benefits, the CTs protocols would induce higher cognitive benefits than NW. Moreover, CT-fit should induce higher executive benefits than the two other training programs, thanks to the inclusion of cognitive stimulation through MwT conditions.

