## 2. Materials and Methods

### 2.1. Study Design

The study is a monocentric randomized trial. Training interventions will be carried out at the “Stade Marseillais Université Club” (SMUC, Marseille, France) that is, a multisport club proposing programs of physical activity adapted to older adults. All subjects must give their informed consent for inclusion before they participate in the study. The study will be conducted in accordance with the Declaration of Helsinki, and the protocol has been approved by the French National Ethics Committee (CPP IDF10 no. 2019-A03263-54) (registered also on ClinicalTrials.gov ID: NCT04504643). Pre- and post-tests will be carried out before and after the training period to evaluate the cognitive, physical, and motor benefits of each program. An evaluation will be done at the Institute of Movement Science (ISM) (Marseille, France).

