
### 2.7. Data Collection and Outcome Measures

Cognitive performance, muscular force, cardiovascular and motor fitness will be assessed before and after the 8 weeks of training. Data collected with the heart rate monitors will be also analyzed, in order to estimate the average intensity of the training interventions (see [27], for a similar procedure).

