### 2.8. Cognitive Assessment

Global cognitive status will be evaluated through the Montreal Cognitive Assessment (MoCA). This test is composed of different subparts and it is highly sensitive to detect MCI. Alternate versions of this test will be randomly assigned ipre- and post-test to each participant, in order to avoid test-retest effects [47]. Executive functions will be assessed through three different tests directed to: inhibition, switching, and working memory respectively. Inhibition processes will be tested with the Stroop test. Participants are seated in front of a computer and requested to indicate the color of the word appearing on the screen by pressing as quickly as possible on the corresponding key of the keyboard while inhibiting the word’s semantic. Four different colors can be presented: green, blue, red, and yellow. Thus, depending on the consistency between the semantic and the color, the condition is considered either congruent (C, e.g., the word “green” written in green) or incongruent (I, e.g., the word “green” written in red). In other trials, “neutral” words (N) are presented (N, e.g., arm, leg...), which are written in one of the different colors. After familiarization with 9 random words, 75 words will be presented for the test. Response times, that is, the time elapsing between the appearance of the word on the screen and manual pressing of the key on the keyboard, will be recorded. Each word remains present on the screen until the response is given. The mean response times (RT, in milliseconds) of the three different conditions will be calculated and compared between the others. Values above the ± 2SD of mean RT will be considered as outliers and excluded. *Switching capacities* will be evaluated through the Trail Making Test (TMT), which is composed of two parts, A and B, respectively. Part A requires participants to draw lines sequentially to connect 25 encircled numbers distributed on a sheet of paper. Part B requires participants to connect alternate numbers and letters (e.g., 1, A, 2, B, 3, C, etc.) with respect to the chronological and alphabetic order [48]. Total execution time (in milliseconds) and the number of errors will be recorded. Switching capacities are quantified by the ratio of the scores obtained in part-B divided by the scores obtained in part-A. Working memory will be assessed with a computerized test developed by the company HappyNeuron™ (Lyon, France), which is composed of two sequential parts. At first, a list of numbers will be provided to the participants via audio-speakers, and subsequently, a list of syllables. Once the full list is played, the participants are asked to repeat the last three items listened. Participants are informed that they cannot ask to listen to the track several times. The test starts with a familiarization trial. The examiner registers the correct answer and goes on with the trials. The time of completion (in seconds) and the total number of points will be recorded. Visuospatial capacities will be tested using the Rey Complex Figure copy task [49]. A complex figure comprising 18 graphic elements, a blank sheet (to copy), and a stopwatch are needed to run the test. The figure is placed in front of the participant, who must reproduce it to the best of his or her ability. The figure is exposed to the subject for a minimum of two and a half minutes and a maximum of five minutes, although it is not removed if the subject exceeds this time. The participant is allowed to copy the figure with a pen, and he/she can self-correct if he/she wants to. After the participant finishes their copy, the figure is removed. The total time required to copy the figure is measured in seconds and the quality of the response is measured for each of the 18 elements that make up the figure. A score between 0 and 2 points is given for each of these elements (maximum score of 36), depending on their accuracy, possible distortion, and location.

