### 2.13. Statistical Analysis

Data will be analyzed with SPSS (SPSS Inc., Chicago, IL, USA). The statistical analysis will allow us to determine the effects of the three different training programs on the cognitive, motor, and physical variables. The analysis will include subjects who completed all the pre- and post-tests. Data of the pre-test and post-test will be presented using descriptive statistics: mean, standard deviation, and percentage to describe the participants’ characteristics and performance on assessments. Comparisons within and between groups at baseline and post-intervention will be done using repeated measures ANOVA, and Newman-Keuls tests as post hoc analyses. The global Anova carried out between groups will allow testing the existence of a training effect (pre/post) for the different groups. Training is expected to improve performance for the three groups for both cognitive and physical variables.

With respect to the post-comparisons, we predict that no statistical differences should be observed between groups in the pre-test, while differences should be observed in the post-test. Specifically, post-hoc comparisons of the performance in the post-test should allow determining whether, as predicted, CT-fit training leads to greater benefits than the two other training modalities.

Baseline differences between groups will be carried out by observing the % of progress (pre/post-training) in each group, in some relevant measures. Adherence to programs will be measured by the absence rate (in %).

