
### 3.2. Strength and Weakness of the Present Study

Several important theoretical and practical issues are addressed in the present study. The first one lies in the comparison between circuit training protocols based on the association of aerobic exercise, muscular resistance training, and either TwM or MwT situations (i.e., CT-c and CT-fit, respectively). If our hypotheses are confirmed, this study will be the first one to show that MwT circuit training implemented via fitness gaming technologies are more effective multi-domain training protocols in older adults. The effects of the NW training protocol are also of great practical interest. Indeed, the results of our previous study [27] suggested that NW is a cheap and very effective way to improve physical, motor, and cognitive capacities in older adults. Notably, the sanitary situation (i.e., Covid-19) could make it difficult to regroup people over 65 years in closed spaces and then, to carry out the study. Additionally, some participants might be discouraged by the use of new technology in the CT-Fit protocol. However, nowadays they are becoming way more familiar with them. Thus, we do not anticipate that the use of technology will be a problem. On the contrary, it could be a motivating factor. Thus, the superiority of the CT-fit training over the more classical training conditions would allow us to conclude that this type of technology augmented training is among the most effective training to improve cognition and physical functions. These types of exercises would therefore be recommended as an optimal solution for the prevention of older adults’ cognitive and physical decline.

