## 4. Conclusions

The validation of the hypothesis concerning the effectiveness of the CT-fit on the improvement of cognition compared to the CT-c and NW should confirm the effectiveness of incorporating the fitness game. Clearly, the other two training programs should show an improvement in the more stimulated skills (for instance, CT-c should show better performance on DT performance). In addition, this new theoretical framework, based on the incorporation of cognitive stimulation into complex goal-oriented actions, implemented by fitness game technology, will create a new line of reasoning within the vast literature on exergames, for the current time focused on the entertainment component of exergames rather than the creation of related theoretical frameworks. In fact, it would show the need for a specific and controlled physical effort combined with cognitive stimulation, in order to make the game of fitness effective.

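### Section 2.13 reads the pre/post effect as a training effect, but with every arm trained it cannot be separated from retest gain; the between-arm comparison is unaffected

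*Protocol article*

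**What the plan says.** The aim is comparative: "The present experiment aims at comparing the effects on cognitive and motor functions of three types of training programs (NW, CT-c, and CT-fit"). All three programs are active (section 2.6), and no waiting-list, untreated or test-only group is described.

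There are two measurement occasions. Section 2.1: "Pre- and post-tests will be carried out before and after the training period". Section 2.7: outcomes "will be assessed before and after the 8 weeks of training".

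Section 2.13 specifies a repeated-measures ANOVA with Newman-Keuls post hoc tests and interprets it this way: "The global Anova carried out between groups will allow testing the existence of a training effect (pre/post) for the different groups". The next sentence gives the expected result: "Training is expected to improve performance for the three groups for both cognitive and physical variables". The paragraph after that turns to the between-arm question, whether CT-fit does better than the other two programs at post-test.

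Section 2.8 acknowledges retest learning for one instrument. Alternate MoCA versions are randomly assigned to the two occasions "in order to avoid test-retest effects". The article describes no alternate version for the TMT, the working-memory lists or the Rey figure (section 2.8), or for the OTMT (section 2.9.6). The weaknesses in section 3.2 mention neither practice effects nor the lack of an untreated arm.

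**The concern.** A pre/post contrast identifies a training effect only if scores would have stayed the same without training. For cognitive tests repeated after about eight weeks that cannot be taken for granted, and the article's own precaution for the MoCA shows that its authors know this. With every arm trained and only two occasions, no analysis of these data can split the observed change into training and retest gain.

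At stake is the secondary prediction that all three programs improve performance. A significant pre/post effect on, say, the TMT or the Rey figure would be read under section 2.13 as evidence that training works, when repetition of the test alone could have produced it. The affected tests bear on executive and visuospatial function, where sections 3 and 3.1 place much of the trial's interest.

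**Working it through.** **Step 1. Reproduce the plan's sample size, to see which test it serves.** Inputs from section 2.12: f = 0.25, α = 0.05, power 0.80, stated N = 42; three groups and m = 2 occasions. The pre/post correlation r is not given; r = 0.5 is assumed. For the group-by-time interaction:

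λ = f² · N · m / (1 − r) = 0.0625 × 42 × 2 / 0.5 = 10.5, with 2 and 39 degrees of freedom.

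The power is 0.803, and 42 is the smallest multiple of three that reaches 0.80. At the same r, the pre/post (within) effect would need 36 and the pure between-group effect 120. So the stated N fits the interaction, which is the comparative question.

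**Step 2. How often is the pooled pre/post effect significant when training does nothing?** Suppose every arm shares a practice gain d, in SDs of a single score. The SD of a change score is √(2(1 − r)). The pooled test has 1 and 39 degrees of freedom and noncentrality

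λ = N · d² / (2(1 − r)).

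Example: d = 0.3, r = 0.5 gives λ = 42 × 0.09 / 1 = 3.78 and a rejection probability of 0.475. The article gives neither d nor r, so both are assumptions shown over a range:

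| Practice gain d | r = 0.5 | r = 0.7 | r = 0.8 |
|---|---|---|---|
| 0 | 0.050 | 0.050 | 0.050 |
| 0.1 SD | 0.097 | 0.129 | 0.170 |
| 0.2 SD | 0.244 | 0.372 | 0.516 |
| 0.3 SD | 0.475 | 0.687 | 0.850 |

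These are probabilities per outcome. A simulation with 14 per arm and 20,000 runs agrees: for d = 0.3 it gives 0.479 at r = 0.5 and 0.688 at r = 0.7.

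**Step 3. The group-by-time interaction under the same conditions.** A gain common to all arms cancels from the differences between arms. In the same simulation the interaction rejects in 4.7% to 5.2% of runs for d = 0, 0.2, 0.3 and 0.5, which is the nominal level.

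**Step 4. What if the claim needs each arm to be significant separately?** Paired t test, n = 14 per arm, 13 degrees of freedom, noncentrality d√14 / √(2(1 − r)). For d = 0.3 each arm is significant with probability 0.18, 0.27 or 0.38 at r = 0.5, 0.7 or 0.8. The arms are independent, so all three are significant with probability 0.18³ ≈ 0.006, 0.27³ ≈ 0.02 or 0.38³ ≈ 0.05. For d = 0.2 the joint probability is below 1% at every r shown.

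**The case against.** The strongest defence is that the trial is comparative. The directional hypotheses concern CT-fit and CT-c against NW, and CT-fit against both. Randomisation protects those contrasts, and step 3 confirms it. A reader might infer that practice alone could produce the trial's main predicted result, or that the design is invalid. Neither follows; the point reaches only the expectation that every group improves.

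The article also limits practice effects in part. It describes familiarisation for the Stroop and working-memory tests, and it scores switching and dual-task costs as ratios, in which a gain proportional in both parts cancels. This stands as mitigation. But a familiarisation trial addresses learning within a session rather than carry-over between sessions, and a ratio still moves if the harder part benefits more from repetition than the easier one.

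Several stronger readings are not supported:

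- **Only the MoCA has alternate forms.** The article describes them only for the MoCA. A full protocol or test manual may hold others.
- **Motor tests need alternate forms too.** Parallel forms have no clear meaning for balance, gait or stepping times.
- **Regression to the mean inflates the change.** Nobody is selected for low cognitive scores. The cognitive criterion excludes low MMSE scores, so any regression on related tests would tend to run against the predicted gain.
- **A false claim that all three programs work would follow in 48–85% of trials.** Those figures belong to the pooled effect at 0.3 SD. Section 2.13 also provides for within-group comparisons, and if each arm had to be significant the joint probability is about 0.6% to 5% (step 4).
- **The closing statements are part of the same error.** Section 3.2 ("These types of exercises would therefore be recommended as an optimal solution for the prevention") and section 4 ("it would show the need for a specific and controlled physical effort combined with cognitive stimulation") are conditional discussion prose. They fix no analysis and do not depend on retest effects.

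**Conclusion.** The point holds in a limited form. Section 2.13 gives the pre/post effect a meaning that the design cannot support. With all arms trained and two test occasions, the effect is training plus retest gain plus any other change over time, and the TMT, working-memory test, Rey figure and OTMT have no described alternate version.

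With no training effect, the pooled pre/post test would be significant in about 10–17%, 24–52% or 48–85% of trials per outcome for a shared practice gain of 0.1, 0.2 or 0.3 SD, against a nominal 5%. This rests on N = 42 completers, equal practice gain in each arm, and r between 0.5 and 0.8. The absence of an untreated arm and the wording of section 2.13 need no assumption.

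The comparison of CT-fit with CT-c and NW is not affected, nor is the sample size on this account. The correction concerns interpretation and does not call for a redesign.

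**What to change.** 1. In section 2.13, stop describing the pre/post effect as a test of whether training works. Call it pre-to-post change, not separable from retest effects, and report it for each arm with a confidence interval.
2. State that claims of benefit rest only on the between-arm (group-by-time) contrasts. These support statements that one program improved performance more than another, not that any program improved it in absolute terms.
3. Where parallel forms exist for the working-memory lists, the TMT and the Rey figure, counterbalance them across pre- and post-test, as is already planned for the MoCA. Whether such forms are available cannot be checked from the article.

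The first two changes are wording and need no further participants or visits. The third costs the preparation of alternate forms and adds slight between-form noise to the change scores.

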### 2.12. Sample Size

The sample size calculation was performed using G. Power 3.1.9.7 (Kiel, Germany) [59]. In order to detect relevant between groups differences and in the changes from pre- to post-intervention, we calculated a sample size sufficient to detect medium effect sizes. Therefore, f = 0.25, α = 0.05, *p* = 0.80, were chosen to favor clinically significant effect sizes. To test the main hypotheses of the present study, 42 participants, are required. In order to compensate for possible dropouts, 3 more participants will be included. The three groups are composed of 15 participants each.

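### CT-fit superiority is judged on post-test comparisons without adjusting for the pre-test score: valid on average, but imprecise and exposed to chance imbalance at 15 per arm

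*Protocol article*

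**What the plan says.** Section 2.13 (Statistical Analysis) plans a repeated measures ANOVA on the pre- and post-test data with Newman-Keuls post hoc tests. It gives the global ANOVA the role of showing a pre/post training effect in the groups. The superiority question goes to the post hoc step: "post-hoc comparisons of the performance in the post-test should allow determining whether, as predicted, CT-fit training leads to greater benefits" than the other two programs. The sentence before it states the expectation that "no statistical differences should be observed between groups in the pre-test, while differences should be observed in the post-test". One further sentence deals with baseline: "Baseline differences between groups will be carried out by observing the % of progress (pre/post-training) in each group, in some relevant measures". No baseline covariate is mentioned, and the group-by-time interaction is not named as the test of superiority.

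Section 2.12 (Sample Size) aims at between-group differences and pre-to-post changes. It uses "f = 0.25, α = 0.05" and power 0.80, and concludes: "To test the main hypotheses of the present study, 42 participants, are required". Three more are added for dropout, and "The three groups are composed of 15 participants each". Section 2.4 randomizes in permuted blocks of three and mentions no stratification by baseline performance.

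**The concern.** Each outcome is measured before and after training, so each post-test score comes with its own best predictor. A comparison of post-test means that leaves this predictor out has two weaknesses in a trial of this size.

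- **Chance imbalance.** Any difference between arms at the start carries over into the post-test contrast in proportion to the pre/post correlation. An arm that happened to start better can look superior, and a real gain can be hidden if the arm started worse.
- **Lost precision.** Variation between participants that the pre-test could explain stays in the error term.

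Neither safeguard in section 2.13 addresses this. A non-significant pre-test with 15 per arm does not show balance. Percent progress is not an adjustment either: it divides by the noisy baseline, it is affected by regression to the mean, and it is planned only for some measures, which are not named.

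**Working it through.** **Inputs.** From section 2.12: f = 0.25, alpha 0.05, power 0.80, N = 42 (14 per arm), 45 randomized (15 per arm). From section 2.7: two occasions. The pre/post correlation r is not given, so 0.5, 0.7 and 0.8 are assumed throughout. Differences are in units of the between-participant SD, taken as equal at pre- and post-test.

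**1. Reproducing N = 42.** For the group-by-time interaction with m = 2 occasions, the noncentrality is λ = N·f²·m/(1−r), with 2 and N−3 degrees of freedom. At r = 0.5, λ = 42 × 0.0625 × 2/0.5 = 10.5 on 2 and 39 df, giving power 0.803. At N = 39 the power is 0.769, so 42 is the smallest equal-arm total. The alternatives do not give 42: the time effect needs 36, the group main effect 120, and a one-way post-test ANOVA at f = 0.25 needs 159. The trial was therefore apparently sized on the interaction, which section 2.13 does not name as the superiority test.

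**2. How large can a chance baseline gap be?** The standard error of a pairwise baseline difference is √(2/15) = 0.365 SD.
- A given pair differs by more than 0.5 SD with probability 2[1 − Φ(0.5/0.365)] = 0.17.
- Some pair among the three does so with probability about 0.36 (simulation).
- Without multiplicity adjustment, a pairwise gap is significant only beyond t(0.975; 42 df) × 0.365 = 0.74 SD.

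**3. What the gap does to the answer.** With no treatment effect, a baseline gap d shifts the expected post-test contrast by r·d. For d = 0.5 SD the shift is 0.25, 0.35 or 0.40 SD at r = 0.5, 0.7 or 0.8.

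Given the gap, the contrast has standard error √(2/n)·√(1−r²), while the test uses √(2/n). With n = 14 and d = 0.7 SD, which is still non-significant (the threshold at 14 per arm is 0.76 SD), the conditional two-sided false-positive rate by normal approximation is 0.12, 0.18 or 0.21. For a small gap of 0.3 SD it is below nominal: 0.04, 0.03 or 0.01. These rates average to 5% over all allocations.

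**4. Change scores do not remove the gap.** Under no treatment effect, the expected difference in change is −(1−r)·d. For d = 0.5 SD this is −0.25, −0.15 or −0.10 SD, an error in the opposite direction. Dividing the change by the baseline does not cancel it.

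**5. Precision.** The relative variance of a between-arm contrast is 1 for post-test only, 2(1−r) for change, and 1−r² for ANCOVA. The detectable pairwise difference uses 14 per arm, 80% power, two-sided 5% and the noncentral t, with 39 df (38 for ANCOVA):

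| r (assumed) | Variance, change | Variance, ANCOVA | Detectable, post-test only | Detectable, change | Detectable, ANCOVA |
|---|---|---|---|---|---|
| 0.5 | 1.00 | 0.75 | 1.09 SD | 1.09 SD | 0.94 SD |
| 0.7 | 0.60 | 0.51 | 1.09 SD | 0.84 SD | 0.78 SD |
| 0.8 | 0.40 | 0.36 | 1.09 SD | 0.69 SD | 0.65 SD |

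**6. Secondary, conditional point on Newman-Keuls.** Suppose the procedure were run across all six group-by-time cells with the within-subject error term. That term is too small for contrasts between different people. In simulation with 15 per arm, no arm difference and a gain common to all arms, at least one false positive among the three post-test contrasts occurs in about 13% (gain 0.3 SD) to 20% (gain 2 SD) of trials at r = 0.5, and in 30% to 38% at r = 0.7. Section 2.13 states neither the six-cell scope nor the error term.

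**The case against.** The strongest defence is that the planned comparison is legitimate. In a randomized trial, a post-test contrast with the right error term is unbiased over allocations and holds its nominal error rate. That stands: the imbalance problem is conditional on the one allocation obtained, and the remainder is a matter of efficiency.

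The baseline is also not absent from the plan. The repeated measures ANOVA contains a group-by-time interaction, the sample size matches it, and section 3.1 frames several hypotheses as larger improvements. This softens the point without removing it. The text gives the superiority decision to the post-test comparisons, and the interaction would itself be no more precise than post-test only at r = 0.5 and less precise than ANCOVA at each r shown.

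Four stronger readings are tempting, and the documents do not support them.

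- **That a non-significant pre-test is a gate for the claim.** It is worded as a prediction, and no step depends on it.
- **That the measures for percent progress will be picked after seeing the data.** The wording is vague, but does not say this. A purely descriptive use is equally possible.
- **That Newman-Keuls will inflate the error rate.** That needs the two unstated choices in step 6, and its size depends on an assumed r and an assumed common gain.
- **That the trial is far too small because a post-test ANOVA at f = 0.25 needs 159.** An interaction f of 0.25 with equal baselines corresponds to a post-test f of 0.50. Then λ = 42 × 0.25 = 10.5, and post-test power is again 0.80.

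A fuller analysis plan might add a covariate. The choice of the post-test comparison is nevertheless this article's own statement.

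**Conclusion.** The point holds as a matter of precision and conditional imbalance. Section 2.13 rests the CT-fit claim on an unadjusted post-test comparison and leaves unnamed the test on which the sample size appears to be based. At 15 per arm, a baseline gap above 0.5 SD between some pair of arms has a probability of about 0.36 for each outcome. Pairwise gaps up to about 0.74 SD pass as non-significant, so the predicted quiet pre-test says little about balance.

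Adjustment would cut the variance of the contrast by 25%, 49% or 64% at r = 0.5, 0.7 or 0.8. Those gains rest on assumed correlations, equal SDs at both occasions and 14 completers per arm. The reproduction of N = 42 also rests on r = 0.5. Because the planned comparison is not invalid, this is a change that should be made and not one on which the trial's validity depends.

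**What to change.** In section 2.13, replace the Newman-Keuls post-test comparisons as the basis for the superiority claim. For each outcome, fit an ANCOVA of the post-test value on arm and pre-test value. Estimate CT-fit minus CT-c and CT-fit minus NW with 95% confidence intervals and a multiplicity adjustment such as Holm.

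Report baseline means and SDs, and percent progress if wanted, descriptively only. Do not read a non-significant pre-test as evidence of balance. If any repeated measures post hoc comparisons are kept, state which cells they cover and which error term they use.

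The cost is analysis wording and one degree of freedom. No new data are needed, because the pre-test is already collected.
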